# Oral medicinal cannabinoids to relieve symptom burden in the palliative care of patients with advanced cancer: a double-blind, placebo-controlled, randomised clinical trial of efficacy and safety of 1:1 delta-9-tetrahydrocannabinol (THC) and cannabidiol (CBD)

**DOI:** 10.1186/s13063-020-04541-6

**Published:** 2020-07-06

**Keywords:** Cannabis, Cannabidiol, Cancer, Symptom control, RCT, Palliative care, THC

## Abstract

**Background:**

Despite improvements in medical care, patients with advanced cancer still experience substantial symptom distress. There is increasing interest in the use of medicinal cannabinoids but little high-quality evidence to guide clinicians. This study aims to define the role of a 1:1 delta-9-tetrahydrocannabinol/cannabidiol (THC/CBD) cannabinoid preparation in the management of symptom burden in patients with advanced cancer undergoing standard palliative care.

**Methods and design:**

One hundred fifty participants will be recruited from five sites within the Queensland Palliative Care Research Group (QPCRG) and randomly assigned to an active treatment or placebo group. This study is a pragmatic multicentre, randomised, placebo-controlled, two-arm trial of escalating doses of an oral 1:1 THC/CBD cannabinoid preparation. It will compare efficacy and safety outcomes of a titrated dose (10 mg/10 mg/mL oral solution formulation, dose range 2.5 mg/2.5 mg–30 mg/30 mg/day) against placebo. There is a 2-week patient-determined titration phase, using escalating doses of 1:1 THC/CBD or placebo, to reach a dose that achieves symptom relief with tolerable side effects. This is then followed by a further 2-week assessment period on the stable dose determined in collaboration with clinicians. The primary objective is to assess the effect of escalating doses of a 1:1 THC/CBD cannabinoid preparation against placebo on change in total symptom score, with secondary objectives including establishing a patient-determined effective dose, the change in total physical and emotional sores, global impression of change, anxiety and depression, opioid use, quality of life and adverse effects.

**Discussion:**

This will be the first placebo-controlled clinical trial to rigorously evaluate the efficacy, safety and acceptability of 1:1 THC/CBD for symptom relief in advanced cancer patients. This study will allow the medical community to have some evidence to present to patients wishing to access cannabis for their symptoms caused by advanced malignancy.

**Trial registration:**

ACTRN, ACTRN12619000037101. Registered on 14 January 2019.

Trial Sponsor: Mater Misericordiae Limited (MML) and Mater Medical Research Institute Limited (MMRI)—[name]

## Background

Despite improvements in medical care, patients with advanced cancer still experience substantial symptom distress [1]. Palliative care aims to take a skilled, holistic approach to improve patients’ symptoms and quality of life. Whilst there is a range of analgesic medication available for pain management, the control of many other symptoms (e.g. fatigue, anorexia, weight loss) remains a challenge [2].

There has been increasing interest in the use of medicinal cannabinoids over recent years, particularly for the relief of symptoms in palliative care patients [3]. Recent legislative change in several Australian states provided pathways for the use of medicinal cannabinoids for a range of indications including chemotherapy-induced nausea and vomiting (CINV), resistant epilepsy, pain and spasticity in multiple sclerosis, and symptoms associated with terminal illness [4].

Cannabis contains almost 500 bioactive compounds, including over 70 different cannabinoids [5]. The predominant cannabinoids include delta-9-tetrahydrocannabinol (THC) and cannabidiol (CBD). THC is the main psychoactive component of cannabinoids and is thought to act as a partial agonist on the endocannabinoid system. Potential benefits of THC include analgesia, anti-nausea and muscle relaxation, with potential side effects including intoxication, psychosis, anxiety and sedation. The recommended dose range for oral THC varies from 2.5 to 40 mg/day [6]. In contrast, CBD is not intoxicating and has a range of anxiolytic, antipsychotic, anti-inflammatory, anti-oxidative, anti-convulsant and neuroprotective effects [7]. CBD is also considered to mediate many of the adverse psychotropic effects of THC, although this research is still emerging [8]. CBD has been used with a dosing in the range of 40 to 1280 mg/day orally [9].

There is little high-quality evidence of benefit to date for the use of medicinal cannabinoids. The most recent review from the USA National Academies of Sciences, Engineering, and Medicine found substantial evidence for the use of medicinal cannabinoids for treatment of some types of chronic pain, CINV and spasticity in multiple sclerosis in some patients, with moderate evidence for sleep disorders [10]. Cannabinoid products are licenced for a range of conditions in different countries, with little consistency between countries for indication and dosing [11]. Whilst cannabinoids may have clinical indication, their use is not without potential for substantial harms, and further research is needed to define their role in medical practice [3, 11].

There are many unknowns when it comes to prescribing medicinal cannabis [11]. This includes the formulation of the drug (ratios of THC or CBD), the dosing of the drug and the best route of delivery. Ongoing concerns remain around the uncertainty over the optimal formulation, toxicity and abuse potential. The 1:1 THC/CBD ratio used in formulations may deliver sufficient CBD to ameliorate the psychotoxic effects of THC but is unlikely to produce significant CBD therapeutic effects.

To date, there has been no formal examination of the effect of different THC/CBD ratios. We will therefore compare efficacy and safety outcomes of a 1:1 THC/CBD formulation against placebo, with doses of both THC and CBD escalated to doses previously shown to be safe.

## Methods

### Aims and objectives

This study aims to define the role of cannabinoids in the management of symptoms in patients with advanced cancer, who are receiving standard palliative care. The hypothesis is that medicinal cannabinoids will reduce the total symptom burden in these patients compared to placebo.

The primary objective is to assess the effect of escalating doses of a 1:1 THC/CBD cannabinoid preparation against placebo on total symptom score at day 14 as measured by the Edmonton Symptom Assessment Scale (ESAS) (change in score from baseline). Secondary objectives are to establish a patient-determined effective dose of a 1:1 THC/CBD formulation and assess the effect on symptom scores at days 7, 21 and 28. Other secondary objectives include assessing the change in total physical and emotional sores, global impression of change, anxiety and depression, opioid use and quality of life at the same time points and to document adverse effects associated with cannabinoid use.

### Study design

This study is a pragmatic multicentre, randomised, placebo-controlled, two-arm parallel trial of escalating doses of oral THC/CBD 10 mg/10 mg/mL oral solution. There is a 2-week patient-determined titration phase, using escalating doses of a 1:1 THC/CBD combination or placebo, to reach a dose that achieves symptom relief with tolerable side effects. This is followed by a further 2-week assessment period on the stable dose determined in collaboration with clinicians.

Eligible patients will be randomly assigned in equal numbers to one of the two study arms. Randomisation schedules will be developed for each site using random number tables, computer generated at an independent centre. Treatment for each patient will be allocated according to a permuted block randomisation schedule held by the central registry. Block randomisation within each centre will ensure even allocation to each arm in each site. The pharmacy will be notified of a participant, and a completed script with the participant’s study ID number will be given to the site pharmacy. The pharmacist will randomise the participant according to the schedule and dispense the medication in a labelled bottle. The participant ID, allocation number, date of request, preparation and dispensing will be recorded in a log maintained by the site pharmacist for each randomisation.

All participants, caregivers, investigators and clinical staff will remain blind to study assignment until trial completion. The code will only be broken in cases of a clinical emergency. An investigator not directly involved in the randomisation of patients will keep an un-blinded copy of the randomisation schedule and will be contacted in the event of the need to un-blind. All study drugs and placebo will be in oil solution form and identical in appearance. All oil solutions will be matched for taste, colour and bottle size to preserve the blinding irrespective of the contents; each participant will receive the oil solution in a prepacked bottle labelled with their individual trial participation ID number and consecutively numbered according to the randomisation scale.

### Intervention

Cannabinoid oils, supplied by LG Pharma, will be used in this study. The decision to use oils was based on a number of factors including product availability, ability to access ongoing supplies, ability to produce matched placebo, regulations surrounding the production and transport of cannabinoid products and cost.

Arm 1 of the trial consists of THC/CBD 10 mg/10 mg/mL oral solution (LG Pharma Pty Ltd) with a dose range of 2.5 mg/2.5 mg–30 mg/30 mg/day and arm 2 a matching placebo oral oil solution. Participants are asked to take daily doses as per dosing schedule instructions. The study drug is to commence on the day of baseline assessment, continuing for a maximum of 28 days.

The cannabinoid oils and placebo will be dispensed in identical 50-mL bottles containing a sufficient quantity of oil. Bottles are to be stored at room temperature (25 °C) until used and stored away from light. The product will be dispensed from bottles with a wadded child-resistant cap. Participants will be given replacement bottles to complete the study as required. Participants will be educated on how to administer daily doses using supplied 1-mL syringes appropriate for the dose. The participant will complete a daily dosing schedule diary at home to record medication taken. Cannabinoid oil that has been allocated to a participant and not used will be returned to the research nurse/research officer and destroyed by the local pharmacy as per pharmacy guidelines.

Dose titration will be confirmed following regular consultation. Each participant will be advised to increase their dose according to a schedule every 2 days until they are satisfied with their symptom improvement or they experience unacceptable side effects. Dose titration downwards will also be allowed, in consultation with research staff. The participant in collaboration with research staff will define the dose level at which they will continue until the primary outcome point (14 days). Participants will then be given the option of remaining on the blinded oil solution for a further 2 weeks (28 days total) for continuing assessment of efficacy and adverse events (continue final dose if perceived to be of benefit and tolerated). Assessment at 28 days following 14 days of stable dose is a secondary end point.

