### Assessments

Participants will receive 2 times/weekly research nurse phone calls in the first 2 weeks and outpatient clinic medical review visits at days 7, 14, 21 and 28, with outcome measures recorded at these points.

Symptom burden will be measured using the Edmonton Symptom Assessment Scale (ESAS). Confirmed documented disease status will be assessed at days 14 and 28, where applicable.

A routine haematology and biochemistry screen including liver function tests will be taken at eligibility/baseline assessment. Blood for C-reactive protein (CRP) as a basic test of inflammation will be taken at baseline, day 14 and day 28. All consenting participants will have a urine test to confirm nil recent use of THC-related products as a pre-screen. Female participants of childbearing potential will have a urine test to determine pregnancy. At day 14, a urine sample will be collected and stored (frozen) until the completion and un-blinding of the study. Samples will be stored on site and transported to central storage in batches over the course of the study. These samples will be for post-trial analysis for evidence of no THC product use during the trial.

Participants will be contacted at day 56 (+ 4 weeks post last dose) for the purposes of safety follow-up and recording of post-study cannabinoid use. Date of death will be recorded for all participants up to the census point. This protocol has been written in accordance with the Standard Protocol Items: Recommendations for Interventional Trials (SPIRIT) (Table 1).

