### Outcomes and assessment tools

The primary outcome is the change from baseline of total ESAS TSDS at day 14.

The ESAS is a 9-item inventory rated on an 11-point scale anchored at 0 (no problem) to 10 (worst problem). It assesses both physical and psychological symptoms, plus general wellbeing. It has been validated in the assessment of symptoms in cancer patients [13].

Secondary outcomes include:
Patient-determined effective dose of THC/CBD formulation, defined as the dose that achieves symptom relief with acceptable side effects.ESAS TSDS at days 7, 21 and 28.Physical and emotional ESAS scores at each time point.
Physical scores will be measured by the Australia-modified Karnofsky Performance Status (AKPS) and Resource Utilisation Groups-Activities of Daily Living Scale (RUG-ADL). The AKPS is a validated variant of the Karnofsky Performance Status. The Australian version can be applied to both in- and outpatients and is sensitive to changes in function over time [14]. The RUG-ADL is an instrument developed for the measurement of nursing dependency. The ADL scale measures patients’ needs for assistance in activities of daily living (eating, bed mobility, transferring and toileting) [17].Individual symptom scores (descriptive analysis only).Oral morphine equivalent (OME), average use at baseline and weekly.Patient Global Impression of Change (PGIC), days 7, 14, 21 and 28.
This is a subjective measure of symptom change completed by the patients themselves [18].Clinical Global Impressions (CGI) Scale, days 7, 14, 21 and 28.
This is a subjective measure of symptom change completed by the investigating clinician [18].The Depression, Anxiety, Stress Scale (DASS-21) score baseline and days 14 and 28.
DASS-21 is a self-reported 21-item scale, 7 questions per sub-item questionnaire measuring depression, anxiety and stress. The DASS-21 will be used for assessment at baseline (day 0) and days 14 and 28 [19].EORTC score QoL baseline and days 14 and 28 [20].This is a QoL measure found valid for use in a wide variety of cancer populations. To reduce patient burden, we will use the 15-question subset commonly used for the palliative care population.NCI common terminology for adverse events V4.03, days 2, 4, 7, 9, 11, 14, 16, 18, 21, 23, 25 and 28 [21]

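### The protocol does not settle whether participants who stop the oil at day 14 are still assessed at days 21 and 28, which puts those secondary comparisons at risk of selection bias

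*Protocol article*

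**What the plan says.** The protocol article describes the second fortnight in two ways.

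**As optional and conditional.** Under Intervention: "Participants will then be given the option of remaining on the blinded oil solution for a further 2 weeks (28 days total) for continuing assessment". The sentence names efficacy and adverse events as what is to be assessed and adds the condition "continue final dose if perceived to be of benefit and tolerated". The section closes with "Assessment at 28 days following 14 days of stable dose is a secondary end point".

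**As part of the schedule for participants generally.**
- Study design mentions no option: "This is followed by a further 2-week assessment period on the stable dose determined in collaboration with clinicians".
- Aims and objectives makes the later time points secondary efficacy objectives: "assess the effect on symptom scores at days 7, 21 and 28".
- Assessments schedules "outpatient clinic medical review visits at days 7, 14, 21 and 28, with outcome measures recorded at these points", with no condition of still taking the oil.
- Outcomes and assessment tools lists the total symptom score at days 21 and 28, several other measures at those days, and adverse events on days 16, 18, 21, 23, 25 and 28, again without condition.

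The primary outcome comes before the choice: "The primary outcome is the change from baseline of total ESAS TSDS at day 14". Statistical analysis and sample size plans mixed models for the repeatedly measured secondary outcomes, allowing for within-subject correlation and centre.

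**The concern.** Perceived benefit and tolerability are known only after randomisation, and both can differ by arm. If the option to keep taking the oil is also the gateway to later assessment, the people measured at days 21 and 28 are selected on early response. Comparing continuers on active treatment with continuers on placebo is then no longer a comparison of randomised groups. Placebo continuers would be those who felt better on placebo, so both arms could appear to show sustained benefit while the difference between them shifts. Adverse events after day 14 would be seen mainly in people who had already tolerated the oil. Those who stopped would next be heard from at the day-56 safety contact.

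This matters at the protocol stage because it concerns data collection. An analysis plan written later can choose a model, but it cannot recover visits that did not take place.

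**Working it through.** **1. The passages side by side.** In Intervention, the grammatical object of the option is staying on the oil, which is a treatment choice. Two features tie it to assessment: the stated purpose of staying on is further assessment, and the day-28 endpoint is described as following 14 days of stable dose, which someone who stops at day 14 cannot have had. Assessments and Outcomes carry no such condition. No section says whether those who decline the oil are still seen at days 21 and 28, and none limits the analysis to continuers. Both readings are open to a site.

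**2. The plan's own figure.** Inputs from Statistical analysis and sample size: difference 6, SD 11.6, two-sided 5%, power 80%, attrition 20%.

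n per arm = 2 × (1.960 + 0.842)² × 11.6² / 6² = 58.7, so 59; the t-test version gives 59.65, so 60. Then 60 / 0.80 = 75 per arm, 150 in total. The stated size reproduces. It concerns day 14 and is not in dispute.

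**3. Size of the shift if only continuers were compared, unadjusted.** From the protocol: difference 6 and SD 11.6, taken as the SD of change. Assumed, not in the documents: mean placebo change −3, active −9 at day 14; day-14/day-28 correlation ρ of 0.4 to 0.8; three continuation rules driven by day-14 change (negative = improvement).

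For a rule of continuing if day-14 change is at most c, with a = (c − μ₁₄)/11.6:

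mean day-28 change in continuers = μ₂₈ − ρ × 11.6 × φ(a)/Φ(a)

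Worked case, c = 0, ρ = 0.6:
- Placebo: a = 3/11.6 = 0.259, φ/Φ = 0.386/0.602 = 0.641, mean = −3 − 0.6 × 7.43 = −7.46.
- Active: a = 9/11.6 = 0.776, φ/Φ = 0.295/0.781 = 0.378, mean = −9 − 0.6 × 4.38 = −11.63.
- Difference: −11.63 − (−7.46) = −4.17, against a true −6.

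Simulation with 2 million per arm gives the same value for this case. Continuer-only differences for a true −6:

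| Continuation rule | Placebo / active continuing | ρ = 0.4 | ρ = 0.6 | ρ = 0.8 |
|---|---|---|---|---|
| Change ≤ 0 | 60% / 78% | −4.79 | −4.17 | −3.56 |
| Change ≤ −6 | 40% / 60% | −4.45 | −3.71 | −2.94 |
| Logistic in change | 58% / 72% | −5.29 | −4.99 | −4.65 |

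The range is 2.9 to 5.3 points. With no true difference at day 28 (but a 6-point effect at day 14), the same comparison shows 0.7 to 3.1 points against active treatment.

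**4. What a model using everyone's day-14 data recovers.** Day-28 change was regressed on day-14 change among continuers within each arm, then averaged over all randomised. This stands in for a likelihood-based mixed model under missing at random. The result is −5.96 to −6.01 for a true −6, and within 0.05 of zero for a true null. The shift disappears because, by construction, stopping depends only on the observed day-14 score.

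**5. What that model does not recover.** Suppose any improvement leads to continuing, and active participants who stop lose their 6-point benefit. The day-28 difference in all randomised participants is −6 × 0.78 = −4.7. A missing-at-random model fitted with continuers' day-28 data still gives −6.0, because it describes what would happen had everyone stayed on the oil. Without day-28 data from those who stopped, the two cannot be told apart.

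**The case against.** The tempting stronger reading is that the day-21 and day-28 comparisons are made in responders and are therefore biased. The documents do not support it:

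- No section restricts collection or analysis to continuers. Assessments schedules the later visits for participants without condition. The schedule table is not shown, and the full protocol behind the article may settle the point.
- The criterion is perceived benefit together with tolerability, in either arm. That is not a responder definition, and the cut-offs used above are assumptions.
- The 3-to-5-point figure belongs to an unadjusted continuer comparison, which the plan does not propose. Mixed models can use earlier scores from those who stop, and step 4 shows the shift vanishing under missing at random. ESAS, the global impression scales and adverse events are all recorded up to day 14, so much of what drives the choice is measured.
- Harms during titration are captured in everyone, and there is a day-56 safety contact. Fewer events after stopping a drug is expected and is not in itself understatement.

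All of this stands, and it limits the point to a risk. It does not dispose of it. The sections conflict as printed, which is different from leaving detail to a later document. Perceived benefit and tolerability need not be fully captured by the symptom scores in the model. And no model supplies outcomes after the oil is stopped if nobody records them.

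**Conclusion.** The point holds as an unresolved conflict that creates a risk of selection bias in the day-21 and day-28 secondary comparisons and in the adverse-event data for days 16 to 28. Bias is not established: it depends on whether those who stop are followed and on why they stop. Its direction is not fixed either, although it ran against active treatment in every scenario tried.

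Under the assumed placebo change, correlations and continuation rules, a raw continuer-only comparison would show a true 6-point difference as roughly 3 to 5 points. The planned mixed models can remove this if stopping depends only on observed scores, but not if it depends on unobserved outcomes. The day-14 primary comparison and the sample size are unaffected. The change is worth making because it is cheap and missed visits cannot be recovered later.

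**What to change.** Reconcile Study design, Intervention and Assessments, and state that:

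1. ESAS, the other scheduled outcomes and adverse events after day 14, including days 21 and 28, are collected in every randomised participant, on or off the oil, unless consent for follow-up is withdrawn.
2. The day-21 and day-28 comparisons are made in all randomised participants, with the effect being estimated named for those who stop the oil.
3. Results in continuers only are labelled descriptive.

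The description of the day-28 endpoint should be reworded so that it can also be met by someone no longer taking the oil. The participant's option to stay on or stop the oil is unchanged.

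The cost is protocol wording plus some extra follow-up contacts, by phone where needed, for participants who stop. The visits are already scheduled.
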